## 9.2 Analytical plan

Data analysis will be primarily performed by the project epidemiologist using SPSS and STATA statistical software packages, with additional assistance from collaborators in San Francisco and the University of California, Berkeley, Department of Epidemiology.

Descriptive statistics will be used to summarise baseline characteristics of study patients. Because age is a strong effect modifier in malaria, an age-stratified subgroup analysis for efficacy outcomes is planned. Study subjects will be stratified by age (< 5 years and > 5 years) for analysis of treatment outcomes. Results for the two age groups will be presented independently. Data on efficacy data will be evaluated using a per-protocol analysis and will only included patients with treatment outcomes. Categorical variables will be compared between the treatment groups using chi-square tests or Fisher’s exact tests and continuous variables will be compared using t-tests. A p-value of < 0.05 will be considered significant. The risk of clinical and parasitological treatment failure after adjustment by genotyping shall be estimated using Kaplan-Meier survival analysis technique in accordance with the 2003 WHO protocol [26]. Data will be censored for new infections.

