### 4.3 Randomization:

Computer generated randomization lists will be created for each of the 4 study sites by a member of the project who will not be directly involved in the conduct of the study. Sealed copies of the original randomization lists and documentation of the procedure used to generate the lists will be stored in the project administrative offices in Kampala. Prior to the onset of the study, sealed copies of the randomization lists will be distributed to the study nurse responsible for treatment allocation.

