# 9.0 STATISTICAL CONSIDERATIONS

## 9.1 Sample size calculations

The sample size calculations will be made for the study based on the estimated efficacy of the combination regimens to be studied in the given regions. For the purposes of sample size calculation, the risk of clinical rescue therapy will be the primary outcome. If the null hypothesis states that there is no difference in clinical outcome between the treatment groups, we plan to test the alternative hypothesis that treatment with an alternative combination regimen will decrease the likelihood of clinical failure at 28 days of follow-up. The risk of clinical rescue therapy with AQ+AS is estimated to be 40-50% based on previous data (UMSP, unpublished data). We plan to enroll 200 patients in each treatment arm at all of the study sites (400 patients per site, 1600 patients total). Based on an α = 0.05 (two-sided) and a power of 80%, allowing for 10% loss to follow-up, we will have the ability to detect a risk difference of approximately 15% between the two treatment groups.

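### The 15-point detectable difference in 9.1 is a one-site figure stated as a trial figure, and 9.2 names tests that do not use the site strata

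*Protocol*

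**What the plan says.** On size, section 9.1 states: "We plan to enroll 200 patients in each treatment arm at all of the study sites (400 patients per site, 1600 patients total". It sets the operating characteristics as "Based on an α = 0.05 (two-sided) and a power of 80%, allowing for 10% loss to follow-up" and concludes that "we will have the ability to detect a risk difference of approximately 15% between the two treatment groups". The reference risk is given as "The risk of clinical rescue therapy with AQ+AS is estimated to be 40-50% based on previous data", and the alternative is that "treatment with an alternative combination regimen will decrease the likelihood of clinical failure at 28 days of follow-up".

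On allocation, section 4.3 says: "Computer generated randomization lists will be created for each of the 4 study sites".

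On analysis, section 4.2.2 promises pairwise comparisons of the regimens on a per-protocol basis. Section 9.2 names chi-square or Fisher tests between treatment groups, with "A p-value of < 0.05 will be considered significant". It also plans a subgroup analysis by age, under and over 5 years, and says "Results for the two age groups will be presented independently". Neither section says whether arms are compared within each site, over all sites, or over all sites with stratification. No expected age split is given.

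**The concern.** The detectable difference follows directly after the total of 1600, so it reads as a property of the whole trial. If it were, it would be wrong by a factor of about two. If it belongs to one site, the protocol should say so, because the reader then needs a second figure for the comparison that uses all the patients.

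The analysis section does not settle the matter. The tests it names carry no site term, although site is the stratum used for randomisation and is likely to be prognostic. Table 1 reports earlier AQ+AS clinical rescue risks of 16% (Kampala), 19% (Jinja), 28% (Apac) and 55% (Tororo). The Ministry of Health is to use these data for drug policy, so it matters whether a difference of 8 or 10 points was within the trial's reach.

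**Working it through.** **Inputs from 9.1:** two-sided alpha 0.05 (z = 1.96), power 80% (z = 0.8416), 10% loss, AQ+AS risk 40-50%, comparator 15 points lower, 200 per arm per site. Evaluable per arm: 200 × 0.9 = 180 at one site, and 4 × 180 = 720 over four.

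**Formula (pooled variance), n per arm:** n = [1.96 √(2p̄(1−p̄)) + 0.8416 √(p₁(1−p₁) + p₂(1−p₂))]² / (p₁−p₂)².

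**Reproducing the plan's figure**

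- 50% vs 35%: p̄ = 0.425. n = [1.96 × 0.6991 + 0.8416 × 0.6910]² / 0.0225 = 3.81 / 0.0225 = 169.3, so 170; 170 / 0.9 gives 189 enrolled.
- 45% vs 30%: n = 163, or 182 enrolled.
- 40% vs 25%: n = 152, or 169 enrolled.
- With a continuity correction the enrolled numbers are 204, 196 and 184.

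The planned 200 per arm therefore fits one site with all ages.

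**Difference detectable at 80% power, same formula, AQ+AS risk 40% to 50%**

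| Comparison | Evaluable per arm | Detectable difference (points) | Power for 15 points |
|---|---|---|---|
| One site, all ages | 180 | 13.9-14.6 (14.4-15.1 corrected) | 82-86% (79-84% corrected) |
| Four sites, all ages | 720 | 7.1-7.4 | above 99.9% |
| One age group, four sites, even split | 360 | 10.0-10.4 | 98-99% |
| One age group, one site, even split | 90 | 19.1-20.3 | 53-58% |

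The first two rows differ by a factor of two because 720 is four times 180 and the difference scales with 1/√n.

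The even age split is an assumption. Within one site, an age group holding 30% of patients has 35-38% power for 15 points, and one holding 80% has 73-78%. Pooled over sites, an age group holding only 25% still has 0.25 × 720 = 180 per arm, hence 82-86%.

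**What stratifying by site gains.** With equal-sized sites, stratification removes the between-site variance of the risk from p̄(1−p̄). The proportional reduction in variance is Var(site risks) / [p̄(1−p̄)], applied here to the Table 1 clinical rescue risks.

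- AQ+AS at its four earlier sites (16, 19, 28, 55%): mean 29.5%, variance 0.02363. 0.02363 / (0.295 × 0.705) = 11%.
- CQ+SP at the three trial sites listed in Table 1 (Kanungu 86, Mubende 70, Tororo 75%): mean 77%, variance 0.00447. 0.00447 / (0.77 × 0.23) = 2.5%.
- AQ+SP at the same three sites (53, 44, 45%): mean 47.3%, variance 0.00162. 0.00162 / (0.473 × 0.527) = 0.7%.

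Of the four AQ+AS sites only Tororo is in this trial, and Table 1 covers children under 5. The 11% is therefore a high-end guide. Even so, 11% less variance shortens a detectable difference only by the factor √0.89 = 0.94.

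**The case against.** Sizing per site is a defensible choice. Section 9.1 ties its estimates to efficacy in the study regions, Table 1 reports by site, and Table 2 spans mesoendemic to holoendemic transmission. With equal arms planned at every site, an unstratified overall test is not confounded by site. The choice of estimator and the handling of site are often left to an analysis plan, which may exist and is not shown. All of this stands. It argues for keeping the site results and limits the gain from stratifying. It does not make the figure in 9.1 clear, because that section attaches no unit to the 15 points.

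Two stronger readings are tempting, and neither is supported.

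- A reader might infer that age groups are to be compared within each site, giving eight uncorrected tests of the primary outcome at about 55% power. Section 9.2 never crosses age with site, calls the age analysis a subgroup analysis, and gives no age split. The charge also conflicts with the observation that the named tests carry no site term: tests run within each site do not ignore site.
- A reader might infer that 80% power for 15 points holds only for one site with all ages. It does not. Pooled over sites, power exceeds 80% for the whole trial and for each age group at an even split.

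Nor does the protocol rule out an overall test. Its comparison between treatment groups can be read as one; it is simply not specified.

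**Conclusion.** The point holds as a correction of what the stated figure refers to. About 15 points is right for one site with all ages; for the 1600 patients named beside it, the protocol's own inputs give about 7. The named tests make no use of the site strata, and the unit of comparison is not stated. The overall and per-site figures rest only on inputs given in 9.1. The figures for age groups rest on an assumed split. Low power in an age-by-site cell does not make 9.1 wrong, since no power is claimed there. The consequence is an ambiguous power statement and a modest loss of precision, not an underpowered trial.

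**What to change.** 1. In 9.1, state that about 15 points is the difference detectable at each site (180 evaluable per arm), and that all four sites together (720 per arm) detect about 7 points.
2. In 9.2, define the overall comparison of AQ+AS with coartemether as stratified by site, reported as a Mantel-Haenszel risk difference with a 95% confidence interval. Analyse the two age groups in the same site-stratified way, pooled over sites, and state the assumed age split. At an even split about 10 points is detectable in each.
3. Keep the site-specific results; they need not be demoted. Label any age-by-site result descriptive, noting power for 15 points of about 53-58% at an even split and about 35-78% for strata holding 30-80% of patients.

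The cost is a few sentences and a little more analysis, with no extra patients. The return is a power statement that matches its comparison. The precision gain is small: roughly 2-11% lower variance, and under 1% if site risks are as close as the earlier AQ+SP risks at the trial sites.

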### 4.2.2 Primary outcome

Primary outcome will be based on the risk of clinical rescue therapy. Pairwise comparisons between regimens will be made based on a per-protocol analysis.

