***If any of the responses fall into the shaded area, exclude the patient from the study***

# APPENDIX 3. UMSP ENROLLMENT FORM.

| **enrollment form** | | |
| --- | --- | --- |
| **1. Study**  **Number:** | **2. Treatment**  **Number:** | **3. Start Date:**  ***(dd/mm/yy)*** |

| 4. Patients name: |
| --- |
| 5. Father’s/Husband’s (if married) name: |
| 6. Mother’s/Wife’s (if married) name: |
| 7. Primary caregiver / guardian’s name and relationship (N/A if mother or father): |
| 8. Sub county of residence. |
| 9. Home parish: |
| 10. LC1/village: |
| 11. Home address and localising features: |
| 12. a) Phone number: Yes ___No ___  If yes: b) Phone number (s) and the owner(s): |
| Patient Information |
| 13. Does the patient use malaria preventive measures: Yes ___No ___Unknown ____  If yes, which measures are used?    a) Spray: Yes ___No ___  b) Coils: Yes ___No ___  c) Chemoprophylaxis: Yes ___No ___  If yes, which drug? ___________________________________  d) Bed net: Yes ___No ____  If yes, is the net treated? Yes ___No ___   How often does the patient sleep under the net?  Always____ Often \ Sometimes____  e) Other protective measures ______________________________________________________________ |

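### Section 9.2 offers only an unadjusted test and separate age-group results, so any all-ages or all-sites comparison of the primary outcome would ignore the strata, at a modest cost in precision

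*Protocol*

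**What the plan says.** Protocol 4.2.2 sets the endpoint: "Primary outcome will be based on the risk of clinical rescue therapy". Section 4.2.1 defines it as early treatment failure plus late clinical failure, so it is binary. For binary outcomes, 9.2 states: "Categorical variables will be compared between the treatment groups using chi-square tests", with Fisher's test as the alternative. No covariate, site term or stratified test appears anywhere. The efficacy analysis is per protocol and uses only patients with a classified outcome.

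On age, 9.2 gives the reason, "Because age is a strong effect modifier in malaria, an age-stratified subgroup analysis for efficacy outcomes is planned", and the method, "Study subjects will be stratified by age (< 5 years and > 5 years) for analysis of treatment outcomes". It then has the two groups reported separately and does not say how they would be combined.

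On allocation, 4.3 states: "Computer generated randomization lists will be created for each of the 4 study sites". Neither age nor parasite density is named as a randomisation stratum. Section 9.1 plans 200 patients per arm at every site, 1,600 in all, to detect a difference of about 15 points. The document does not say whether the primary comparison is made site by site or over all four sites.

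Age and Day 0 parasite density are on the case record forms (Appendix 12), and bed net use is on the enrolment form (Appendix 3).

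**The concern.** A comparison that leaves out a prognostic stratum has a larger standard error than the same data allow. Here the protocol names one such factor itself (age) and randomises within another (site). Yet 9.2 provides only two kinds of result: separate results by age group, each on part of the sample, and, if an overall figure is wanted, a crude one. The sample size in 9.1 assumes all 200 patients per arm at a site contribute to one comparison, so an all-ages result is implicitly expected. What is missing is a single estimate that uses all patients and respects the strata. At stake are some precision in that estimate and a prior commitment to how the strata are combined.

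**Working it through.** **Inputs.** From Protocol 9.1: two-sided alpha 0.05, 80% power, AQ+AS risk 40-50%, difference about 15 points, 200 per arm per site, 10% loss. That leaves n = 200 × 0.9 = 180 per arm per site. From Table 1: clinical rescue risks by site. The protocol gives no association of age, density or net use with outcome, so the share s of outcome variance they explain is an assumption, shown as a range.

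**Step 1: reproduce the plan's figure.** With d = p1 − p2 and p̄ = (p1 + p2)/2:

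power = Φ{[d − 1.96·√(2p̄(1−p̄)/n)] / √([p1(1−p1) + p2(1−p2)]/n)}.

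For 50% v 35% and n = 180: null SE = √(2 × 0.425 × 0.575/180) = 0.0521; alternative SE = √((0.25 + 0.2275)/180) = 0.0515; power = Φ[(0.15 − 1.96 × 0.0521)/0.0515] = 82.4%. At control risks of 45% and 40%, power is 83.9% and 86.3%. The difference detectable with 80% power is 13.9, 14.3 and 14.6 points at 40, 45 and 50%. This matches the stated 15 points, but only as a per-site calculation. Pooled over four sites (720 per arm) the detectable difference is about 7 points.

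**Step 2: gain from adjustment.** Explaining a share s multiplies the variance by (1 − s), which acts like n = 180/(1 − s).

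| Assumed s | SE factor √(1−s) | Power at 40 / 45 / 50% | Detectable difference at 50% |
|---|---|---|---|
| 0 | 1 | 86.3 / 83.9 / 82.4% | 14.6 points |
| 2% | 0.990 | 86.9 / 84.7 / 83.1% | 14.4 |
| 5% | 0.975 | 87.9 / 85.7 / 84.3% | 14.2 |
| 10% | 0.949 | 89.6 / 87.5 / 86.1% | 13.8 |

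The gain is about 0.6-0.8 points of power at s = 2% and 3.3-3.7 points at s = 10%.

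**Step 3: age groups reported without a combined result.** If half the patients are under 5 (assumed), each age group at a site has 90 per arm. Power for a 15-point difference is then 58 / 55 / 53% at control risks 40 / 45 / 50%, against 86 / 84 / 82% for all ages.

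**Step 4: site, relevant only to a pooled test.** Site share of variance = var(site risks)/[p̄(1−p̄)].

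- AQ+SP at Kanungu, Mubende and Tororo (53, 44, 45%), all trial sites: 0.00162/0.2493 = 0.7%. Arua has no data.
- AQ+AS at Kampala, Jinja, Apac and Tororo (16, 19, 28, 55%): 0.0236/0.2080 = 11.4%. Only Tororo is a site of this trial.

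With arms balanced within site, the crude pooled test has true two-sided size 2·[1 − Φ(1.96/√(1−s))]. This is 4.9% at s = 0.7% and 3.7% at s = 11.4%. Simulation with 180 per arm per site over four patterns of site risk gave 3.1-5.0%. The test stays valid, and is clearly conservative only when site risks differ widely.

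**The case against.** The strongest reply is that nothing in 9.2 is wrong. The crude test is valid, delivers the planned power without adjustment, and fits a design sized site by site, where no site term is needed. All of that stands.

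A reader might infer that chance age imbalance contaminates the planned results. The documents do not support this. Section 9.2 already splits patients at 5 years, which removes imbalance between the two groups. What could remain is imbalance within 1-4 and 5-10 years, or imbalance in a crude all-ages figure if one is reported. Nor would it be an extra error. With half under 5 and an assumed age gap of 20-30 points, the between-arm difference in the share under 5 has SD √(2 × 0.25/180) = 5.3 points. That moves the risk difference by SD 1.1-1.6 points. The crude SE of about 5.2 points already contains this: (1.05/5.16)² = 4.2% and (1.58/5.16)² = 9.4%, the same as the variance shares those age gaps imply.

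A reader might also infer that ignoring site wastes the equivalent of 13% more patients (1/(1 − 0.114) = 1.13). That rests mainly on sites outside this trial and applies only to a pooled test.

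It can also be said that covariate choice belongs in an analysis plan that is not shown. That would excuse silence, but 9.2 names the test. Finally, a Mantel-Haenszel estimate averages an effect that the protocol expects to differ by age. That is fair, and is why the age-specific results should stay.

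**Conclusion.** The point holds as a matter of efficiency and of a missing combined estimate. It is not an error in the result. Section 9.2 fixes an unadjusted test and separate age-group results, and provides no all-ages or all-sites estimate that respects the site lists and the age grouping. The benefit of supplying one is modest: about 0.6-4 points of power at 180 per arm if covariates explain 2-10% of outcome variance. That share is assumed, because the protocol gives no covariate-outcome data and Table 1 covers only children under 5. The site component is nil for per-site tests and probably small for a pooled test (0.7% on the trial-site data, though for a different regimen and without Arua). Randomisation is by site only, so it should not be read as stratified by age as well. No claim is made for bed net use, whose relation to outcome is not documented. The change is worth making because it costs almost nothing and settles in advance which combined result is primary.

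**What to change.** In 9.2:

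- Keep the age-specific results as planned.
- For any all-ages result within a site, use a Mantel-Haenszel risk difference with a Cochran-Mantel-Haenszel test stratified by age group.
- For any result pooled over sites, stratify by site and age group.
- As an alternative, prespecify a logistic model with treatment, age, log10 Day 0 parasite density and, if pooled, site, reported as a standardised risk difference.
- Say whether the primary comparison is per site or pooled, and show the crude result beside the stratified or adjusted one.

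The cost is a few sentences in 9.2 and slightly more analysis work. Site, age and Day 0 density are already collected. The drawback is an effect averaged over age groups, which the retained age-specific results offset.

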### 4.2.3 Secondary outcomes

1. Risk of clinical treatment failure
2. Risk of parasitological rescue therapy
3. Risk parasitological treatment failure
4. Risk of fever during the first 3 days of follow-up: presence or absence of objective fever (axillary temperature > 37.5C) or patient report of fever on days 1, 2, 3
5. Risk of parasitemia on follow-up days 2 and 3: proportion of positive vs. negative thick blood smears on day 2 and day 3
6. Change in mean haemoglobin from day 0 to 28 or day of repeat therapy
7. Proportion of subjects lacking gametocytes on day 0 with gametocytaemia on any follow-up day
8. Risk of serious adverse events: proportion of patients experiencing any serious adverse event in each treatment group during the 28-day follow-up period, excluding treatment failures
9. Risk of adverse events of moderate or greater severity, at least possibly related to the study medications, excluding treatment failures.

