# 6.0 BASELINE EVALUATION AND TREATMENT ALLOCATION

## 6.1 Baseline evaluation and procedures

On day 0, patients fulfilling the selection criteria will be assigned a study number and will undergo a complete history and physical examination (Appendix 9). Patients will be referred to the laboratory to obtain a fingerprick blood sample for repeat thick blood smear, thin blood smear, haemoglobin measurement and to save of filter paper for future molecular testing. After going to the laboratory, the patients will be referred to the study nurse for treatment.

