# 7.0 FOLLOW-UP EVALUATION AND PROCEDURES

## 7.1 Follow-up schedule

Patients will be asked to return to the clinic for follow-up on days 1, 2, 3, 7, 14, 21, 28, and any unscheduled day that they feel ill. All patients will be reimbursed the cost of their transport to and from the clinic. At enrolment, details about the location of the patient’s residence will be obtained and if a subject does not return for a scheduled clinic follow-up appointment, the study personnel shall visit them at home. Patients who return on day 1 and fail to fulfil the criteria of *P. falciparum* mono-infection with a parasite density of > 2000 parasites/ul and < 200,000 parasites/ul will be excluded from further study and referred to OPD for management. At each repeat visit, temperature will be measured and a focused physical examination will be performed. A finger prick blood sample will be obtained on days 2, 3, 7, 14, 21 and 28 (and any extra day) to repeat thick blood smears and to save on filter paper. Haemoglobin will be re-evaluated on day 28 or at the time of clinical treatment failure.

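### Secondary outcome 6 (haemoglobin) is to be tested by an unadjusted t-test on change: valid, but less precise than adjusting for the day-0 value already collected

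*Protocol*

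**What the plan says.** The outcome is item 6 of nine in Protocol section 4.2.3: "Change in mean haemoglobin from day 0 to 28 or day of repeat therapy". The section 1 summary lists the same outcome.

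The method comes from a general rule in section 9.2: "continuous variables will be compared using t-tests". No covariate, analysis of covariance or regression model for any outcome appears in the protocol. Section 9.2 does plan separate presentation of two age groups for efficacy outcomes, but that is not adjustment for baseline haemoglobin.

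The baseline value is available for everyone. Section 6.1 includes it in the day-0 fingerprick ("thin blood smear, haemoglobin measurement and to save of filter paper for future molecular testing"), and Table 4 marks it for day 0. There is one later value, under section 7.1: "Haemoglobin will be re-evaluated on day 28 or at the time of clinical treatment failure".

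For efficacy data, the analysed set is "evaluated using a per-protocol analysis and will only included patients with treatment outcomes" (section 9.2). The sample size in section 9.1 is built on clinical rescue therapy only. No SD, target difference or power is given for haemoglobin.

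**The concern.** A change score subtracts the whole of the baseline value, which amounts to fixing the slope of final on baseline haemoglobin at 1. In practice that slope is usually below 1 because of regression to the mean. Section 6.6 gives a further reason to expect it here: children below 10 g/dL receive iron, so recovery is likely to depend on the starting value.

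When the slope is below 1, the t-test on change has two weaknesses. It leaves variance in the comparison that the day-0 value could remove. It also over-corrects: an arm that happens to start lower will tend to show the larger rise whatever the drug does. What is at stake is the width of the interval for one secondary outcome, and how far its estimate depends on the luck of the day-0 balance. The primary outcome is not affected.

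**Working it through.** **The plan's own figure.** There is none for haemoglobin, so the only figure to reproduce is the one for clinical rescue therapy. Inputs from section 9.1: "We plan to enroll 200 patients in each treatment arm at all of the study sites"; "Based on an α = 0.05 (two-sided) and a power of 80%, allowing for 10% loss to follow-up"; "The risk of clinical rescue therapy with AQ+AS is estimated to be 40-50% based on previous data". Evaluable patients per arm per site: 200 × 0.9 = 180. With 180 per arm and 80% power, the detectable reductions from 40%, 45% and 50% are 13.9, 14.3 and 14.6 points (14.4, 14.8 and 15.1 with continuity correction). This agrees with the stated figure of about 15%. It also shows that the figure refers to a single site, so 180 per arm is used below.

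**Assumptions, because the documents are silent.** The baseline-to-final correlation r is 0.3, 0.5 or 0.7. The SD s is the same at both times. Where g/dL are needed, s is 1.5 to 2.0 g/dL.

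**Direction, without assuming equal SDs.** Let s0 and s1 be the baseline and final SDs. Per patient:

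- Variance of change = s0² + s1² − 2·r·s0·s1
- Large-sample residual variance after baseline adjustment = s1²(1 − r²)
- Difference = s0² − 2·r·s0·s1 + r²·s1² = (s0 − r·s1)², which is never negative

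The difference is zero only when s0 = r·s1, that is, when the slope r·s1/s0 equals 1. So the direction of the gain does not depend on r or on equal SDs; only its size does.

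**Size, with equal SDs.** The ratio is s²(1 − r²) / [2s²(1 − r)] = (1 + r)/2. Detectable difference at 180 per arm, in SD units, is (1.960 + 0.842) × √(2v/180), with v = 2(1 − r) for change and v = 1 − r² for the adjusted analysis.

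| r | Variance ratio (1 + r)/2 | Variance saved | Adjusted n per arm matching 180 on change | Detectable difference, change vs adjusted (SD) | Adjusted power where change has 80% |
|---|---|---|---|---|---|
| 0.3 | 0.65 | 35% | 117 | 0.349 vs 0.282 | 93.5% |
| 0.5 | 0.75 | 25% | 135 | 0.295 vs 0.256 | 89.9% |
| 0.7 | 0.85 | 15% | 153 | 0.229 vs 0.211 | 86.0% |

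A simulation of 20,000 trials with 180 per arm gave variance ratios of 0.65, 0.76 and 0.85.

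**Sensitivity to chance imbalance.** With equal SDs, the difference in change keeps (r − 1) times the day-0 difference between arms. In the simulation, the change-score estimate correlated with the day-0 imbalance at −0.59, −0.49 and −0.39 for the three values of r; the adjusted estimate correlated at about 0. A chance imbalance at its 95% limit is 1.96 × √(2/180) = 0.207 SD, or 0.31 g/dL (s = 1.5) to 0.41 g/dL (s = 2.0). The resulting shift, in the opposite direction, runs from 0.3 × 0.31 = 0.09 g/dL (r = 0.7, s = 1.5) to 0.7 × 0.41 = 0.29 g/dL (r = 0.3, s = 2.0). If the four sites were pooled (4 × 180 = 720 per arm), the imbalance and the shift would halve, to about 0.05 to 0.14 g/dL. The variance ratio would not change.

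**The case against.** The strongest reply is that nothing here is wrong. A t-test on change in a randomised comparison holds its type I error and is unbiased on average. The outcome is one of nine secondary outcomes, with no stated power or threshold, so nothing shows that the lost precision would alter a conclusion. The sentence in 9.2 is generic, and an analysis plan that is not shown might add covariates. All of this limits the severity. It does not remove the point: the generic sentence, read with item 6, does name a method, and a better use of data already collected costs nothing.

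The size can also be challenged. Both r and equal SDs are assumptions. Final values mix recovered children on day 28 with children who are ill on the day of failure, so a single SD and a single r are doubtful. If the slope came close to 1, the gain would be negligible. Iron below a cut-off is also a threshold effect, which a straight line in baseline only approximates. That stands as a caution about the percentages and about how completely an imbalance is removed. It does not change the direction of the large-sample result.

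Four stronger readings are tempting, and the documents support none of them.

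- A reader might infer that the planned test is biased. It is not, on average; the over-correction is conditional on a chance imbalance having occurred.
- A reader might infer from section 9.1 that up to half of all patients have their final reading early, during a new malaria episode. The 40–50% is the AQ+AS estimate. If the other arm is 15 points lower (25–35%), the two-arm average is 32.5–42.5%. Clinical rescue as defined in section 4.2.1 also includes early failures and recrudescences, which are not new infections, and a late clinical failure found on day 28 is not early.
- A reader might infer that leaving out site is an error. The protocol does not say that haemoglobin will be pooled, and within one site a site term has no meaning.
- A reader might infer that adjustment deals with the variable time of the final reading. It does not, because that time depends on outcome under either analysis.

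**Conclusion.** The point holds as a free improvement to a secondary outcome. Sections 4.2.3 (item 6) and 9.2 together set an unadjusted t-test on change. Day-0 haemoglobin is in hand for every enrolled patient, and using it as a covariate is more precise in large samples unless the slope of final on baseline is exactly 1. The saving is about 35% to 15% of the variance for correlations of 0.3 to 0.7 with equal SDs, neither of which the documents give. Adjustment also largely frees the estimate from chance day-0 imbalance, to the extent that a straight line describes the baseline relation. The planned t-test remains valid, and no conclusion on the primary outcome depends on this.

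**What to change.** In section 9.2, state that outcome 6 will be analysed by a linear model of final haemoglobin (or, equivalently for the treatment effect, change) on treatment and day-0 haemoglobin, reporting the adjusted mean difference with its 95% CI. Add site as a factor when sites are pooled. Where results are reported by the planned age strata, fit the model within each stratum.

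Day-28 and day-of-failure values may be tabulated separately, labelled as description only: those groups are formed after randomisation, and the adjustment does not correct for the timing of the reading.

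The cost is one or two sentences. SPSS and STATA, already named in 9.2, fit this model, and no extra patients, visits or measurements are needed. Fixing it in advance also prevents a later decision to adjust that could be driven by the data.
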